### Power and sample size calculation

Using sample means from baseline and the end of the treatment phase of the OM consumption data from our pilot study [19], we estimate that a total sample size of 316 will provide 80% power using a 1% level of significance to detect an effect size estimate of 0.48 between the EA and sham EA groups. Because intention-to-treat analysis will be used, no additional participants are required. We plan to recruit 316 participants in total. A dropout rate of 20% is considered to be within the normal range.

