### Randomisation and blinding procedures

After a four-week run-in period, participants who meet all selection criteria are randomly allocated into one of the three groups, namely EA, sham EA or no-EA with a 2:1:1 ratio. An automated telephone randomisation service provided by the National Health and Medical Research Council Clinical Trial Centre at the University of Sydney is used. Before the commencement of the first acupuncture session, the treating acupuncturist dials a toll-free number and enters the identification codes of the trial, the acupuncturist and the site, and the baseline OM weekly dose (morphine equivalent). The participant is then randomly allocated to one of the three groups according to a computer-generated randomisation sequence. The acupuncturist records the allocation in a secure and separate file. The computer-generated randomisation uses stratified permuted blocks to ensure that an equal ratio of participants in EA and sham EA groups in each centre is assigned to each acupuncturist; and to ensure that an equal number of participants consuming high or low dose of OM is assigned to each group. The cut-off OM dose for high or low consumption is 560 mg (morphine equivalents) per week, decided upon by pain specialists on the team based on our pilot study and other published studies reporting average OM consumption by patients with chronic pain [22,23]. Three quarters of the participants are in either the EA or sham EA group and are blinded; one quarter of the participants are in the no-EA group and are be blinded. The success of blinding of the two acupuncture groups is assessed. Details are presented in Assessment of efficacy below.

The acupuncturists and MDs are not involved in outcome assessments. Blinded assessors are required to conduct outcome assessments, collect Medication and Pain Diaries, and check any missing data. The trial data are entered by research assistants and analysed by a statistician. Except for the acupuncturists, all of the above will be are blinded to participant allocation. Professional statistical assistance is also sought to double check the data analysis.

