### Pain medication management

PMM is an integral part of pain management in multidisciplinary clinics. In this trial, PMM consists of patient education about pain and pain medications, and advice on OM reduction. A *Pain and Medication Management Information Brochure* has been developed to standardise PMM across all centres. In the fifth week, MDs explains to participants the impact of chronic pain, and the potential problems associated with OMs. OM reduction schedules are developed and explained to each participant at the interview. The schedule is flexible and individually tailored. It includes instructions for which type of OM to reduce first, how much and when, the alternative medications and what to do if pain increases. In general, short-acting OMs are reduced first, then the long-acting (slow-release) OMs. Participants are asked to reduce their OM dosage by 30% in week 8, 50% by week 11 and 75% to 100% by Week 14. Participants are asked to reduce OM as long as their pain is not worse. If increased pain causes distress or dysfunction, participants can increase their OM dose to the previous level or take alternative non-opioid medications prescribed by MDs. Clonidine may be prescribed for participants experiencing opioid withdrawal symptoms as judged by the MDs. The dosages of all pain relief medications are recorded.

As part of PMM, during the 10-week treatment and the three-month follow-up periods, a trained researcher will make a phone call to all participants three times during the treatment and once a month during the follow-up period to remind participants of the OM reduction schedule. During the trial period, participants are instructed to continue their routine therapies.

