### Withdrawal

Participants who find their pain significantly worse or cannot tolerate EA may terminate their involvement in the study. They are assessed by one of the MDs with advice on alternative management strategies for their condition. Their data will be treated as missing data.

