### Statistical analysis of the trial outcomes

The Statistical Program for Social Science (SPSS, the latest version) is used for data analyses. Baseline categorical data, demographic characteristics such as gender and age category, and numerical data are analysed with *χ*^2^ tests and one-way analysis of variance, respectively, to determine comparability of the three groups on these variables.

Linear mixed models (for continuous outcome variables) and generalised estimating equations (for categorical outcome variables) are used to examine the changes over time in weekly dosage of OM, numbers and types of OM-related AEs, severity of pain and Beck Depression Inventory. *χ*^2^ tests are also used to detect group differences in the numbers of dropouts and AEs.

Both intention-to-treat and per protocol analyses are used. Data from participants who do not violate the treatment protocols will be included in the per protocol analysis. Missing data are dealt with using the last value carried forward method. Missing Beck Depression Inventory and SF-36 data are dealt with according to the relevant manual.

Apart from the effects of types of intervention, the influence on the outcomes of differences between centres and therapists is also analysed. The relationship between OM reduction and attitude to pain are explored.

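### Last value carried forward is fixed for an opioid dose on a planned taper, so the EA–sham contrast can be biased, in an unpredictable direction, when the amount, timing or reason of dropout differs between arms

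*Protocol article*

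**What the plan says.** The rule stands in the protocol article under Statistical analysis of the trial outcomes: "Missing data are dealt with using the last value carried forward method". Missing Beck Depression Inventory and SF-36 data follow their manuals; no exception is made for opioid dose. The same section names linear mixed models for change over time in weekly opioid dose.

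Four other places bear on it:

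- **Taper (Pain medication management).** "Participants are asked to reduce their OM dosage by 30% in week 8, 50% by week 11 and 75% to 100% by Week 14". If increased pain causes distress or dysfunction, "participants can increase their OM dose to the previous level".
- **Withdrawal.** "Participants who find their pain significantly worse or cannot tolerate EA may terminate their involvement in the study". The data of those who leave are then treated as missing.
- **Electroacupuncture interventions.** Participants who complete under half of the 12 sessions are classed as non-compliant, and their data are treated as missing too.
- **Power and sample size calculation.** "A dropout rate of 20% is considered to be within the normal range". No split by arm is given.

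The primary outcome is the change in opioid dose from baseline to the end of treatment. The first secondary outcome is the number of participants with a 50% reduction at the end of treatment and of follow-up.

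**The concern.** Carrying the last value forward assumes that a leaver's dose would have stayed where it was. The protocol asks every arm to move the dose down until week 14, and allows it back up when pain increases. Neither course fits a flat line.

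Two errors follow, with opposite signs:

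- **Early leavers** are frozen near baseline dose. If they would otherwise have tapered further, the arm that loses more of them looks worse than it is.
- **Leavers still on a reduced dose** keep that reduction for good. If they in fact go back up, the arm that loses more of them looks better than it is. Such a person counts as a 50% responder only if the last recorded dose is at most half of baseline.

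The primary EA–sham contrast and the responder comparison then depend partly on who left, when and why. The rules that turn collected data of non-compliant and withdrawn participants into missing data hand more values to this method.

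**Working it through.** **1. The plan's own figure.** Inputs from the article: "we estimate that a total sample size of 316 will provide 80% power using a 1% level of significance" and "to detect an effect size estimate of 0.48 between the EA and sham EA groups", with allocation "namely EA, sham EA or no-EA with a 2:1:1 ratio". This gives 158 EA, 79 sham and 79 no-EA. Sidedness is not stated; two-sided is assumed.

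n(sham) = (2.576 + 0.842)² × (1 + 1/2) / 0.48² = 76.03, so 77, and the total is 4 × 77 = 308 (312 with the t distribution). Power with 79 and 158 is 81.8% (81.1% with t). The stated 316 is reproduced, so the concern is not with the sample size formula.

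**2. Scale (assumed).** The article does not say on what scale 0.48 was computed. If it corresponds to the pilot difference of 39% − 25% = 14 points, the SD is 14 / 0.48 = 29.2, about 29 points. The mean of the two pilot reductions is (39 + 25) / 2 = 32%. The standard error of the EA–sham difference is 29 × √(1/158 + 1/79) = 4.0 points.

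**3. Leavers would have gone on tapering; no true effect.** Let reduction rise linearly to 32% at week 14 and let leaving times be uniform over the treatment period. The average leaver is carried at about 16%, half of 32%. Then

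bias (EA minus sham) = (dropout in sham − dropout in EA) × (32 − 16).

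| Assumed dropout, EA v sham | Overall in these two arms | Bias by formula | Bias, simulated | Error at nominal 1%, simulated |
|---|---|---|---|---|
| 20% v 20% | 20% | 0 | about 0 | 0.8–1.1% |
| 18% v 24% | 20% | 0.06 × 16 = 0.96 | 1.0–1.1 | 1.3% |
| 15% v 30% | 20% | 0.15 × 16 = 2.4 | 2.4–2.7 | 2.5–3.1% |
| 10% v 30% | 16.7% | 0.20 × 16 = 3.2 | 3.2–3.6 | 4.2–4.8% |

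The ranges come from separate simulations that compare week-14 reduction by a t-test. They differ by simulation error and by how leaving times are drawn. Swapping the two dropout rates moves the bias toward sham.

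**4. Leavers really return to baseline dose; no other difference between arms.** Now bias = dropout in EA × carried reduction in EA − dropout in sham × carried reduction in sham.

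- 25% v 15%, both carried at 30%: 0.10 × 30 = 3.0 points toward EA, error 3.4%.
- The same rates, both carried at 50%: 0.10 × 50 = 5.0 points, error 9.2%.
- 20% v 20%, EA carried at 50% and sham at 30%: 0.20 × 20 = 4.0 points, error 5.7%. Equal dropout with different timing is not safe.
- Dose already raised before leaving (carried reduction 0): bias 0.

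In step 3 the arm with more dropout looks worse; here it looks better.

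**5. The 50% outcome.** At 20% dropout there are about 158 × 0.20 = 32 EA and 79 × 0.20 = 16 sham leavers. If none had reached half of baseline, none is counted as a responder through carrying forward. If half of them had, about 16 and 8 are. The schedule sets the 50% target for week 11. A participant on schedule with fewer than six sessions has stopped by about week 7, before the 30% target, and would be carried near baseline as a failure.

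**6. What the mixed model assumes instead.** In the 15% v 30% case, suppose all leavers return to baseline. The true contrast over everyone randomised is then (0.30 − 0.15) × 32 = 4.8 points. Carrying forward gives 2.4–2.7 points. A model in which leavers continue like similar stayers gives about 0. So that model alone does not deal with return to baseline.

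**The case against.** The strongest reply is that the harm rests on assumed dropout gaps. That is largely right: the article gives 20% overall and no more, a gap of 18% v 24% costs little, and at equal dropout and timing the nominal level is held. The simulations also use a t-test on percentage reduction, not the planned mixed model on weekly dose.

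Several stronger readings are tempting, and the document does not support them.

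- **That the bias favours EA because sham participants leave early.** Nothing in the article says so. It reports that participants in the earlier study could not tell EA from sham, and the one treatment-specific reason for withdrawal is intolerance of EA.
- **That unequal dropout always biases the result.** Bias also depends on timing and on the dose leavers would have reached. It can be nil with unequal dropout and present with equal dropout.
- **That failed tapers are in general counted as successes.** This needs a last recorded dose at or below half of baseline. The dose may already have gone back up before the person left.
- **That the 1% level is lost, or that standard errors are too small in general.** The equal-dropout result shows no inflation; the excess error comes from the shift in the mean.

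It is also fair to say that an analysis plan not shown may add sensitivity analyses. But carrying forward is stated here as the method, not left open. A bias of unknown sign cannot be defended as conservative either.

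**Conclusion.** The point holds in this limited form and should be fixed before analysis, because it concerns the primary contrast and the remedy is cheap. The method's assumption of a constant dose conflicts with the protocol's own taper, missingness is tied to pain, and the rule takes in the data of non-compliant and withdrawn participants. The mixed model named beside it can use incomplete series, so filling in is not needed.

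Under the continued-taper assumption the bias runs from about 1 to 3.6 points across the dropout gaps examined, against a pilot difference of 14 points, with error of 1.3% to 4.8% at nominal 1%. These figures rest on an assumed mean of 32%, an SD of 29 points, uniform leaving times and assumed dropout by arm. If leavers return to baseline, the sign reverses for the same dropout imbalance. Confidence is high that the rule is unsuitable. The size and direction in this trial cannot be known from the document.

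**What to change.** 1. For the primary outcome, fit the linear mixed model to all observed weekly opioid doses without carrying values forward, and take the EA–sham contrast at week 14.
2. In the intention-to-treat analysis, include doses recorded by non-compliant or withdrawn participants instead of setting them to missing. Without this step, a model on observed data still omits them.
3. For the 50% outcome, count participants with no week-14 (or week-26) value as non-responders.
4. Add a multiple-imputation sensitivity analysis in which those who withdraw for worse pain are assumed to be back at baseline dose. The mixed model treats leavers as continuing like similar stayers, so this case needs its own analysis. It is an assumption for imputation, not a rule for treatment.
5. Keep last value carried forward at most as a further sensitivity analysis.

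The cost is a change of wording, a little more programming and slightly wider confidence intervals.

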## Discussion

CMP is prevalent, with high socioeconomic impacts. OMs have been increasingly prescribed for patients with CMP both in Australia and worldwide. There is, however, no evidence supporting the long-term use of opioids for patients with CMP. Furthermore, OM is associated with severe AEs, which further impact on patients’ quality of life. OM might be a hindrance that prevents patients from taking part in more active management programmes. Effective treatments that reduce OM consumption and related AEs are urgently needed and will benefit both patients and society.

Our pilot study shows that EA, when combined with PMM, is potentially effective in reducing OM usage by patients with chronic non-cancer pain. It also demonstrates the feasibility of a collaborative research involving complementary health professionals, clinicians in pain management, pain researchers and acupuncture researchers. Following the validated protocol, with an expanded team of experts and researchers, the proposed study will for the first time determine whether EA is of significant clinical value in assisting the management of debilitating chronic pain by reducing OM consumption and its associated AEs, as well as improving the quality of life of those with CMP.

Such an outcome will provide a rationale for incorporating EA into existing multidisciplinary pain management programmes. Future research will examine whether a different form of EA, such as non-invasive EA, can be used by patients at home to achieve the same effectiveness.

## Trial status

The trial is open to recruitment and will be completed by the end of December 2012. We expect the results will be published by the end of 2013 or early 2014.

## Abbreviations

AEs: adverse events; CMP: chronic musculoskeletal pain; EA: electroacupuncture; MD: medical doctor; OM: opioid medication; PMM: pain medication management; SF-36: 36-item Short-Form Health Survey version 2.
